### Design

The study is a randomized, double-blind, placebo-controlled, 2-armed, parallel groups clinical trial with children and adolescents randomized to receive either 3 capsules (if less than or equal to 45 kg) or 4 capsules (if greater than 45 kg) of PCSO-524® or placebo.

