#### Exclusion criteria

Medical diagnosis other than ADHD, Oppositional defiant disorder or similar behavioural disorders; Currently taking any medication (other than stimulants if a formal diagnosis of ADHD or other behavioural disorder is present); Current or history of heart disease or high blood pressure or diabetes; Health conditions that would affect food metabolism including the following: food allergies, kidney disease, liver disease and/or gastrointestinal diseases (e.g. Irritable bowel syndrome, coeliac disease, peptic ulcers); Pregnant or breast feeding; Unable to participate in all scheduled visits, treatment plan, tests and other trial procedures according to the protocol; Allergy to shellfish; Epilepsy or photosensitive.

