#### Power and statistical analysis

The sample size for this study is 150 participants with 75 participants in each arm (Lyprinol vs Placebo). A power calculation to determine the sample size was performed using Gpower 3.12. Based on previous studies looking at omega-3 supplementation in children with ADHD such as Sinn & Bryan (2007) who had an *n* of 132 and were able to find statistical significance in terms of the CPRS [15], a small to medium effect size (F = .20) on the Conners’ was postulated for Lyprinol over placebo from baseline to week 18 over six time points (critical F = 3.92, with an alpha probability of 0.05 and beta power of 0.80). This provided a sample size of 118; with drop-outs being projects at approximately 20%, a sample of 150 participants was estimated. Repeated Measures ANOVAs with an *n* of 150 (75 per group) will allow the researchers to account for any confounding variables in the trial including within-group and between-group variability. Any heterogeneous variables showing statistically significant differences at baseline will be co-varied in order to negate their influence on the power of the study.

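### Covariates are chosen by baseline significance tests, so baseline CPRS is almost never used as a covariate; the main cost is power, not overall false-positive error

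*Protocol article*

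**What the plan says.** The rule, with its reason, is in the protocol article under Power and statistical analysis: "Any heterogeneous variables showing statistically significant differences at baseline will be co-varied in order to negate their influence on the power of the study". The planned model is repeated measures ANOVA, and no covariate is named for inclusion whatever the baseline tests show. The variables to be tested at baseline are not listed.

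The effect is postulated "from baseline to week 18 over six time points", so the baseline CPRS score counts as one of the six outcome values. Randomization and safety describes computer-generated random allocation and names no stratification factor.

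The sample is mixed by design. Ages run from 6 to 14. Medication is excluded "other than stimulants if a formal diagnosis of ADHD or other behavioural disorder is present". The number of capsules depends on weight: "3 capsules (if less than or equal to 45 kg) or 4 capsules (if greater than 45 kg").

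**The concern.** A baseline significance test after randomisation asks whether a difference arose by chance, and the answer is already known to be yes. Whether adjustment helps depends on how strongly the variable predicts the outcome, which the test does not measure. The stated reason is therefore mistaken: a covariate gains power through its correlation with the outcome, not through a significant imbalance.

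Three consequences follow.
- A strong predictor is left out in about 19 trials of 20, and an irrelevant variable enters if it happens to cross the threshold.
- The primary model is unknown until the baseline data have been tested, and the set of tested variables is open.
- If baseline CPRS is the variable that differs, it would stand on both sides of the model.

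At stake are the power of the primary comparison and, in trials with an imbalance just short of significance, the trustworthiness of the unadjusted result.

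**Working it through.** **Inputs.** From Power and statistical analysis: f = 0.20 (d = 0.40 for two arms), alpha 0.05, power 0.80, six time points, critical F 3.92, N = 118 before dropout and 150 after. Assumed: a common correlation ρ between CPRS scores, not stated in the article (0.5 reproduces the plan; 0.3 to 0.7 shown); SD 1; no difference at baseline and 0.40 SD at each of the five later times; p<0.05 for the baseline tests; 118 analysed.

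**The plan's own figure.** For the between-group main effect, λ = f²·N·m / (1 + (m−1)ρ) = 0.04 × 118 × 6 / (1 + 5 × 0.5) = 28.32 / 3.5 = 8.09. With F on 1 and 116 degrees of freedom, the critical value is 3.92 and power 0.805; N = 116 gives 0.799. So 118 is reproduced, and 118 / 0.8 = 147.5, close to the planned 150. The group-by-time version would give N = 28 and critical F 2.28, which does not match. The sample size therefore rests on the main effect over all six times, baseline included.

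**How often the rule acts.** Under randomisation a given variable is significant at p<0.05 in 5% of trials; simulation gave 5.0%.

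**Power.** Standard error = √(4v/118), with v as follows:
- Mean of six times: (1+5ρ)/6, with the true difference diluted to 0.40 × 5/6 = 0.333.
- Post-baseline mean: v5 = (1+4ρ)/5.
- Change from baseline: v5 + 1 − 2ρ.
- Post-baseline mean adjusted for baseline: v5 − ρ².

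At ρ = 0.5, the adjusted analysis has v = 0.6 − 0.25 = 0.35, standard error 0.109 and ratio 0.40/0.109 = 3.67, hence power 0.954. The main effect has v = 0.583, standard error 0.141 and ratio 0.333/0.141 = 2.37, hence power 0.652.

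| Analysis (118 analysed) | ρ = 0.3 | ρ = 0.5 | ρ = 0.7 |
|---|---|---|---|
| Six-time main effect, no covariate | 0.794 | 0.652 | 0.545 |
| Six-time main effect, stated rule (simulated) | 0.81 | 0.68 | 0.57 |
| Change from baseline, no covariate | 0.652 | 0.794 | 0.949 |
| Change from baseline, stated rule (simulated) | 0.67 | 0.81 | 0.95 |
| Post-baseline mean, no covariate | 0.901 | 0.794 | 0.695 |
| Post-baseline mean, baseline CPRS always a covariate | 0.954 | 0.954 | 0.986 |

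Simulation put the last cell at about 0.98. The rule adds only 2 to 3 points to the unadjusted main effect because it so rarely acts.

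Not all of the gap in the main-effect rows is due to the covariate rule. At ρ = 0.5 the rule applied to the post-baseline mean gives about 0.82. So of the 27 points between 0.68 and 0.95, about 13 remain once baseline is no longer averaged into the outcome. The other 14 or so come from the averaging.

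**Type I error.** Over all trials the rule gives 0.032 (main effect) and 0.038 (post-baseline mean) at ρ = 0.5, against 0.050 with constant adjustment. For the main effect at ρ = 0.5, given a baseline imbalance of z = 1.5 or 1.9, the unadjusted error is 0.10 or 0.22. Averaged over baseline |t| between 1.5 and the critical value of 1.98, which occurs in about 9% of trials, it runs from about 7% (single visit, ρ = 0.3) to about 16% by integration, or 18% in one simulation (main effect, ρ = 0.7). Constant adjustment stays at about 5%.

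**Size of an uncorrected imbalance.** At z = 1.9 the gap is 1.9 × √(4/118) = 0.35 SD. At ρ = 0.5 it shifts the unadjusted post-baseline mean by 0.5 × 0.35 = 0.17 SD, against an assumed effect of 0.40 SD.

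**The case against.** The strongest reply has five parts.

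1. **Baseline CPRS is in the analysis.** A reader might infer that it is ignored, or that its imbalance goes wholly uncorrected. The article does not support that: baseline is one of the six repeated outcomes. If the test of interest is group by time, an imbalance is handled much as in a change score, and at ρ = 0.7 little power is lost (about 95% against 98%). This stands. It does not remove the loss at ρ = 0.3 or 0.5, nor does it fit the main effect on which the sample size rests. The full five-degree-of-freedom interaction test has less power still (0.55 at ρ = 0.5).

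2. **Error control is intact.** A reader might infer an inflated false-positive rate. Overall it is at or below 5%, and the shift from imbalance averages to zero over randomisations. This stands; the inflation is conditional only.

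3. **No section shows that age, stimulant use or weight band predicts CPRS.** This stands. They are plausible, not documented, and the calculations cover baseline CPRS alone.

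4. **The trigger uses pre-treatment data, and the treatment code is held outside the project until data collection ends.** This largely answers any suggestion that covariates would be picked to suit the result. What remains is that the candidate variables are not listed.

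5. **A statistical analysis plan may say more.** It may, but the rule is stated outright here. A plan that followed it would carry the fault over, and a sound one would contradict the article.

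**Conclusion.** The concern holds as a poor selection rule with a wrong rationale, whose main cost is efficiency. On the test that reproduces N = 118, the loss against a prespecified baseline adjustment is about 14, 27 or 41 points of power at ρ = 0.3, 0.5 or 0.7 (95−81, 95−68, 98−57), part of it due to averaging baseline into the outcome. On a change-from-baseline reading it is about 28, 14 or 3 points (95−67, 95−81, 98−95). These figures rest on an assumed correlation, equal correlations between all visits, a constant effect after baseline and 118 analysed, so they illustrate the loss and are not the trial's exact power. The rule does not bias the average estimate or raise overall type I error. It should be fixed, but it does not by itself invalidate the primary analysis.

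**What to change.** Delete the sentence that ties adjustment to significant baseline differences, and do no baseline significance tests for choosing covariates. In its place, state that post-baseline scores are the outcome and that the baseline value of that outcome is a covariate in every efficacy model. This also removes the possibility of baseline CPRS being outcome and covariate at once. Name in advance a short list of plausible prognostic variables already collected, for example age and stimulant use; weight band is optional because it overlaps with age. Settle the list before the treatment code is opened.

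The cost is a few degrees of freedom and a change of wording. No new data or participants are needed.

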## Conclusions

Attention-deficit/hyperactivity disorder (ADHD) is the most prevalent developmental disorder in school aged children [1,3]. The symptoms of ADHD include hyperactivity, impulsivity, and inattention. The prevalence rate of ADHD within Western cultures is between 5% and 12%, representing the most common neurodevelopmental disorder among school-aged children, with an estimated 50% of these children retaining ADHD symptoms into adulthood and for the rest of their lives [1,3] and less than 5% of this demographic attaining a university degree [18]. Interventions which are efficacious and which have no or little side effects are urgently required for both children and adolescents who fall within the clinical classification of ADHD and also who have high levels of the symptoms of inattention and impulsivity but who fall below the classification of ADHD. One treatment model is based on the reduced levels of LC-PUFAs in the plasma of ADHD children compared to normals [6,13-15,17]. This has led to extensive research examining the efficacy of omega-3 supplementation as a natural alternative to methylphenidate (MPH e.g., Ritalin®) and other stimulant and non-stimulant pharmaceuticals [16,17]. In the current study we will administer either placebo or a novel and patented marine lipid from the New Zealand Green Lip Mussel (PCSO-524®) to 150 children and adolescents with ADHD or high levels of inattention and hyperactivity for 14 weeks. A range of behavioural and neurophysiological measures will be undertaken. The results of the study will aid our understanding of the role of LC-PUFAs in improving behavioural, cognitive and physiological variables in children and adolescents and whether this intervention is efficacious.
